**Sampling method and subject recruitment (randomization and blinding)**

A single-blind randomized controlled trial design has been chosen. Randomization for the parallel prevention phase will be carried out after checking the inclusion and exclusion criteria. The eligible AD patients will be randomized 1:1:1 ratio to the three arms of the study according to a computer generated, blocked randomization list. The eligible patients will be assigned to the probiotics group, ACT group, and control group with a treatment code concealed in a closed envelope. The randomization will be performed by the study statistician, who had no contact with the patients and not involve in the research project. The statistician is trained to randomize subjects who first enrol in the study into the three groups using computer system for randomization purpose. The allocation sequence will not be available to any member of the research team until databases had been completed and locked. Data collection will be performed by research assistants who were not involved in the study and do not know the objectives of the study. While data analysis will be carried out by the statisticians not involved in the study. Hence, this study is blinded to the researchers but not blinded for the subjects as the ACT group has no parallel control group.

**Data collection and research tools**

In this study, patients with alcohol dependence were given oral probiotics on the basis of conventional treatment. Stool samples and blood samples were collected before and after medication, and the changes of intestinal flora and blood biochemical indexes were analyzed and compared. The EEG changes before and after medication were detected by ERP, and the patients were evaluated regularly with Hamilton Anxiety Scale, Hamilton Depression Scale, alcohol withdrawal Symptom Scale, Pennsylvania Alcohol Desire Scale, etc. To investigate the therapeutic effect of probiotics on patients with alcohol dependence, the changes of intestinal flora and EEG in patients with alcohol dependence. Regular follow-up was performed outside the hospital. The recurrence rate after treatment was analyzed to determine the long-term efficacy of the treatment plan and provide reference and basis for clinical treatment.

***Test drug and treatment plan***

Test drug: Probiotic powder, specification: 2g:0.1g (Probionic Corp., South Korea.).

Placebo drug: Maltodextrin, Specification: 2g:0g (Probionic Corp., South Korea.).

The probiotics, placebo and medications for conventional treatment will be provided by the 2nd Affiliated Hospital of XXMU. There are no other sponsors. The test drug contained both probiotics and prebiotics, and both the test drug and the placebo drug were light yellow powder with no difference in taste. The probiotic powder used in the test drug was maltodextrin as the carrier, which was the same as the placebo drug. Both investigational and placebo drugs should be kept in the temperature range of less than 30 ° C as recommended by the manufacturer.

Treatment: In addition to conventional drug therapy for alcohol dependence, the following interventions were applied to each group:

Routine treatment: alcohol detoxification treatment was carried out at the early stage of admission, mainly with benzodiazepine replacement therapy, while adequate supplementation of B vitamins, strengthening symptomatic supportive treatment, and corresponding antipsychotic drugs, antidepressants or emotional stabilizers were given according to the condition. Benzodiazepines are gradually discontinued after withdrawal symptoms disappear (2 weeks).

Probiotics + conventional drug therapy group: on the basis of conventional drug therapy, probiotics powder 2g, mixed into water or milk, dissolved and oral.

Placebo + conventional drug treatment group: on the basis of conventional drug treatment, maltodextrin of the same weight as the test drug treatment group was mixed into water or milk and orally dissolved.

Frequency of probiotics and placebo treatment: once a day, each time 2g, 8 weeks.

ACT treatment group: Enrolled AD patients will be treated under the ACT protocol for eight weeks. Once a week, each treatment lasted about 1 hour.

***Fecal collection***

Gut microbiota profiles are determined via fecal microbiota analysis. Prior to fecal sample collection, an early announcement will be made one or two weeks earlier and all subjects will be given the fecal collection kit. Materials provided for fecal collection, are fecal collection tube (with RNAlater™ solution and 4 glass beads in tube) and rice paper. A piece of rice paper is floated on water surface in a lavatory bowl (Picture 1). Using the spatula attached to the tube cover, two spatula portions of the feces defecated on the rice paper are collected. Fecal specimens should not be contaminated with water, urine, barium, or mineral oil (Picture 2). Spatula is put back into the fecal collection tube and capped tightly (Picture 3). Then put into ziplock bag, sealed, stored in -80℃ (if possible, can be quick-frozen liquid nitrogen). Fecal sample collection must be completed within one week, upon receiving the fecal collection tube and rice paper. A picture instruction leaflet will be provided prior to fecal collection.

***Questionnaires***

(1) Socio-demographic questionnaire (Chinese version):

This questionnaire covers includes age, marital status, employment, education, monthly income, race, religion, history of medical illnesses, history of psychiatric illness, and history of medication intake, duration of alcohol intake, Average frequency of alcohol intake, average quantity of alcohol intake, and time of last alcohol intake prior to assessment

(2) AUDIT (Chinese version, Figure 1):

This questionnaire can screen drinkers from mild to severe.The reliability and validity of the Chinese version are 0.782. Factor analysis showed that indeed the Chinese version of the AUDIT comprised of three factors and had good convergent and discriminant validity [44]. The scale consists of 10 questions, of which three relate to the amount and frequency of alcohol consumption, three relate to alcohol dependence and four involve in various problems caused by alcohol. The score of the scale ≥ 8 is positive. In general, those with high scores on the first three questions but low scores on the rest suggest serious harmful drinking; High scores in questions 4, 5 and 6 indicate alcohol dependence; High scores in the final section indicate that drinking has caused harm.

(3) CIWA-Ar (Chinese version, Figure 2):

The scale is a standard tool for quantifying the severity of alcohol withdrawal symptoms. The reliability of the Chinese version of CIWA-Ar was good with Cronbach’s α of 0.83 [45]. The total score < 10 suggests mild withdrawal reaction. The score of 10 to 20 indicates moderate. And the total score of more than 20 is considered severe. A severe total score is associated with a risk of delirium tremens and seizures.

(4) VAS (Chinese version, Figure 3):

The VAS has been demonstrated to be accurate for assessment of pain among Chinese patients [46]. It is a simple scale with single factor and single item. A horizontal line corresponding to 0 to 10 points represents the degree of craving from mild to severe. "0" indicates that you don't want to drink at all, and "10" indicates that you really want to drink and cannot restrain yourself. The subjects will be asked to mark the lines according to their perception of themselves.

(5) PACS (Chinese version, Figure 4):

This questionnaire consists of five items to evaluate the severity of craving, including frequency, intensity, duration, difficulty of coping, and average craving degree.The reliability of the Chinese version of PACS was good at Cronbach’s α of 0.97 [47]. It is a seven-point scale from 0 to 6, with 0 being none and 6 being extremely severe. The subjects will be asked to answer questions according to the situation in the past week.

(6) HAMA & HAMD (Chinese version, Figure 5):

These two scales are used to assess the emotional aspects of patients.The reliability of the Chinese version of the HAMD was acceptable with Cronbach’s α of 0.714 [48]. While, the reliability of the Chinese version of the HAMA was 0.93 [49]. HAMA consists of 14 items. The total score ≥ 29 indicates that there may be serious anxiety; The total score ≥ 21 indicates that there must be obvious anxiety; The total score ≥ 14 indicates that there must be anxiety; And the total score ≥ 7 indicates that there may be anxiety. If < 7 points, it is considered that there are no anxiety symptoms. The HAMD we choose is the 24-item version. The total score > 35 indicates severe depression; The total score from 20 to 35 indicates definite depression; And total score from 8 to 20 indicates possible depression. If < 8 points, it is considered normal.

**Figure 1 Figure 2**

**Figure 3 Figure 4**

**Figure 5**

***ERP detection***

(1) Experimental paradigm:

Visual stimuli will be presented by E-Prime 2.0 software. The paradigm consists of three types of images such as i) images related to alcohol cues (common drinking environments, habitual drinking products, etc.), ii) neutral images unrelated to alcohol cues, and iii) task-related images requiring key operation. We will collect EEG while patients watch the stimulation paradigm (Figure 6).

(2) EEG signal acquisition:

We will use the Brain Amp MR-32 instrument to collect signals, and record data through the Brian Vision Recorder software. 64 standard scalp positions will be recorded according to the 10-10 standard lead system (Figure 7). The sampling rate is 1000 Hz, and the impedance between electrode and skin should be less than 5 kΩ.

(3) ERP analysis:

Data will be analyzed using Brian Vision Analyzer 2.1 software. The process includes ① re-reference, ② filtering, ③ removal of ocular artifacts, ④ artifact removal, ⑤ segmentation, ⑥ baseline correction, and ⑦ peak detection.

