**Secondary objectives:**

(1) To determine the differences in the serum levels of pro-inflammatory cytokines among patients on Lactobacillus sp., placebo and ACT, at 4 timelines (baseline, 8 weeks after starting intervention, 12 weeks after starting intervention, and 24 weeks after starting intervention which is 12 weeks post termination of intervention).

(2) To assess the differences in severity of depression and anxiety symptoms among patients on Lactobacillus sp., placebo and ACT via use of questionnaire, at 4 timelines (baseline, 8 weeks after starting intervention, 12 weeks after starting intervention, and 24 weeks after starting intervention which is 12 weeks post termination of intervention).

(3) To investigate the changes of EEG characteristics in patients with AD after the above related treatments, at 3 timelines (baseline, 2 weeks after starting intervention, 8 weeks after starting intervention).

(4) To assess the differences in gut microbiota profiles of patients on Lactobacillus sp., placebo and ACT via the use of fecal samples, at 3 timelines (baseline, 2 weeks after starting intervention, and 8 weeks after starting intervention).

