**2.3 Research Progress of Event-related Potential Technology**

Event-related potential (ERP) is a special evoked EEG. When the body receives multiple or diverse events with psychological significance, there will be a "time-locked" relationship between the EEG and the stimulation, which can reflect the neural electrophysiological phenomenon of the brain in the process of cognitive processing. ERP is an "online window" to observe the mental activities of human brain, which can make objective evaluation of advanced mental activities[36]. In the past, many scholars have used ERP technology to carry out studies on substance addiction, especially in the composition of ERP-P300. P300 is associated with a variety of cognitive processes and is an indicator of a variety of neurocognitive processes, including attention and working memory. Some studies suggest that abnormal ERP amplitude may be a disease marker of substance dependence and a potential neurobiological endophenotype[37]. Bartholow et al. used an experimental paradigm containing images with alcohol cues to detect P300, and found that the P300 response of subjects with low sensitivity to alcohol was significantly enhanced, while that of subjects with high sensitivity to alcohol was not.

Moreover, such enhanced P300 response was alcohol-specific and would not be extended to other motivational related stimuli. Alcohol cue-induced P300 may be a sensitive endophenotype for the risk of alcohol addiction[38]. Petit et al. 's study showed that alcoholics had enhanced ERP responsiveness to alcohol-related cues, especially male patients[39]. Meta-analysis on drug dependence indicated that in the detection of attention preference and craving in drug cue images, the increase of cue-induced P300 amplitude was correlated with the increase of subjects' craving degree[40]. The previous study of our research team[41] found that there were positive results in EEG analysis of AD patients in the craving state induced by static pictures of alcohol cues, that is, AD patients presented lower N200 amplitude and higher P300 amplitude under the stimulation of alcohol cues, which were positively correlated with the subjective craving scale score. It is possible to objectively assess the psychological dependence of AD patients by using alcohol cue response to induce the craving for alcohol and monitoring the task-state EEG (ERP) of the subjects at the same time.

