**Study flowchart**

**Figure 3.1. Flow chart of the study**

**Data analysis**

All data analysis will be performed using SPSS software version 25.0 (SPSS Inc, Chicago, IL, USA). Descriptive statistics for socio-demographic and clinical characteristics, CIWA-Ar, PACS, AUDIT, VAS, HAMD, and HAMA scores, ERP analysis, and serum pro-inflammatory cytokine levels will be computed. All categorical variables will be presented in frequency and percentage, while all continuous variables will be reported in mean and standard deviation or median and interquartile range, depends on normality. Differences in socio-demographic and clinical characteristics between the three groups will be computed with Pearson’s chi square test or one way ANOVA or Kruskal Wallis test.

The mean difference in the primary outcome (CIWA-Ar, PACS, AUDIT, and VAS scores) for the three randomized groups (ACT, probiotic, and palcebo groups) at each specific time point (pre-intervention, 2 weeks at completion of conventional treatment [t0], post-treatment at 8 weeks [t1], post-treatment at 12 weeks [t2], and post-treatment at 24 weeks [t3]) will be assessed using one way analysis of variance (ANOVA) followed by false discovery rate adjustment. For the main pool analysis, mixed ANOVA is used to determine the interaction between the groups (ACT, probiotic, and placebo groups) and time points (t0, t1, t2, and t3) on the primary outcome ( CIWA-Ar, PACS, AUDIT, and VAS scores; interaction = intervention × time; where time is a within-subject variable and intervention effect is a between-subject variable). The main effects of intervention in the groups and time points will be presented as estimated marginal mean and standard error of mean. The study’s primary analysis will follow the intention-to-treat (ITT) principle. The data analysis for the study’s secondary outcomes (severity of anxiety and depressive symptoms, pro-inflammatory cytokines, EEG characteristics, and fecal microbiota) will be conducted similarly to the primary outcomes’ calculation. Statistical significance will be two-tailed and set to p < 0.05.

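### As specified, the EEG analysis does not isolate alcohol-cue reactivity, and its listed measure, a detected peak, grows with recording noise

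*Protocol*

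**What the plan says.** Protocol, ERP detection, item (1): three image types are shown, namely alcohol-cue images together with "neutral images unrelated to alcohol cues, and iii) task-related images requiring key operation".

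Protocol, ERP detection, item (3): the steps are introduced as what the process includes. They start with re-referencing, filtering and two artifact-removal steps, and end with "⑤ segmentation, ⑥ baseline correction, and ⑦ peak detection".

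Protocol, section 2.3, gives the reason for the cue paradigm. Of an earlier study it reports that "such enhanced P300 response was alcohol-specific and would not be extended to other motivational related stimuli", and it goes on to propose the EEG response to alcohol cues as an objective measure of psychological dependence.

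Protocol, Secondary objectives, item (3): EEG characteristics are studied at "baseline, 2 weeks after starting intervention, 8 weeks after starting intervention". No component, image type or contrast is named there.

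Protocol, Data analysis: EEG is handled in the same way as the primary scores, that is, one-way ANOVA at each time point and a mixed ANOVA in which "time is a within-subject variable and intervention effect is a between-subject variable". Image type is not among the factors.

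**The concern.** The rating scales give one score per visit, so group and time are sufficient factors for them. The EEG task gives three responses per visit, and by the protocol's own argument the informative one is the response specific to alcohol images. A group-by-time model with no image type and no stated contrast does not test that. A change in general attention or arousal would appear in the same place as a change in cue-induced craving. ACT works partly through mindfulness, so a non-specific change of this kind in one arm is at least conceivable.

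The second part is the measure. A peak is the largest value in a window of signal plus noise, so its expected size rises with noise and falls as more clean trials are retained. The EEG visits run from admission for untreated alcohol use disorder, through the end of the roughly two-week benzodiazepine course, to week 8. Recording quality may differ between these states. Objective (3) is worded as change after treatment, and the Data collection section describes EEG before and after medication. Such readings would carry any shift in noise with them.

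At stake is how research question 3 is interpreted. The primary outcome and the sample size are not affected.

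**Working it through.** The protocol states no amplitude, SD, trial count or window for the ERP, so there is no figure to reproduce. Apart from the 30 patients per arm and the two-sided 0.05 level, every number below is an assumption.

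**1. Text.** Section 2.3 rests the marker on a response specific to alcohol images. ERP detection collects alcohol and neutral images, so the contrast can be formed. Data analysis names two factors, group and time, and no derived contrast. The stated analysis therefore does not use what the rationale relies on, although the data for it will exist. The EEG visits (baseline, weeks 2 and 8) also differ from the time points of the mixed ANOVA for the scores (weeks 2, 8, 12 and 24), so the EEG model has to be written out separately in any case.

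**2. What the contrast removes.** Let A and N be a patient's alcohol and neutral amplitudes, and g a general shift. The alcohol-only amplitude changes by g. The difference does not change: (A + g) − (N + g) = A − N.
- Simulation with A from 5 to 6.5 µV, N from 3 to 4.5 µV, noise SD 10 µV and 40 trials: the alcohol-only peak moved by 1.34 µV, and the alcohol-minus-neutral difference in window mean by −0.03 µV.
- Limit: if a general change scales both responses instead of adding to them, it shrinks but does not vanish. A 30% gain moves A by 5 × 0.3 = 1.5 µV and the difference by (5 − 3) × 0.3 = 0.6 µV.

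**3. Peak against noise.** Assumed: Gaussian P300 of 5 µV at 350 ms, search window 250–500 ms, baseline −200 to 0 ms, noise low-passed at 30 Hz and averaged over n trials (noise SD = single-trial SD/√n), 4,000 waveforms per setting. Mean detected peak in µV:

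| Single-trial noise SD | 20 trials | 40 trials | 80 trials | Window mean (true 2.87) |
|---|---|---|---|---|
| 5 | 6.24 | 5.80 | 5.49 | 2.87–2.88 |
| 10 | 8.01 | 6.96 | 6.26 | 2.87–2.88 |
| 20 | 12.01 | 9.60 | 8.03 | 2.85–2.87 |

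At SD 10, going from 20 to 80 retained trials with no true change gives a fall of 8.01 − 6.26 = 1.75 µV, or 35% of the 5 µV signal. A second simulation with other assumptions (peak at 380 ms, window 300–500 ms, 1/f noise) gave biases of 2.04 and 3.73 µV at 20 trials and 1.03 and 1.73 µV at 60, for noise SD 10 and 15. The apparent falls are 2.04 − 1.03 = 1.01 and 3.73 − 1.73 = 2.00 µV, or 20–40% of the signal.

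**4. Arm comparison.** 30 per arm (Sample size estimation), no true difference, noise SD 10 µV, between-patient SD 2 µV, two-sided t-test at 0.05, 2,000 replicates. False-positive rate:

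| Retained trials, arm v arm | Peak | Window mean |
|---|---|---|
| 40 v 40 | 4.5% | 4.3% |
| 20 v 20 | 4.8% | 5.6% |
| 40 v 20 | 46% | 5.0% |
| 40 v 10 | 99% | 4.1% |

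The last two rows give every patient in one arm the lower count. They show the mechanism and do not forecast this trial.

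**5. Price of the difference.** With equal SDs and correlation r between the two conditions, SD(difference)/SD(raw) = √(2(1 − r)): 1.00 at r = 0.5, 0.77 at 0.7, 0.63 at 0.8 and 0.45 at 0.9. Below 0.5 the difference is noisier than the raw amplitude. The protocol gives no value for r.

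**The case against.** The strongest reply is that the protocol leaves the EEG variable undefined and does not choose a bad one. An alcohol-minus-neutral difference would fit a group-by-time model, and section 2.3 reports the team's earlier result for alcohol cues specifically. Windows and electrodes can properly sit in an analysis plan or laboratory manual that is not at hand. This stands in part: such detail is not counted as missing here. But the protocol does fix the model and names the peak as its ERP measure, and neither follows from its rationale.

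Three stronger readings are tempting and not supported.
- A reader might infer that trials are never averaged, since averaging is not listed. The list is introduced as what the process includes, so it does not claim to be complete, and averaging is ordinary ERP practice.
- A reader might infer that the trial has no means of separating cue-specific from general responses. Neutral images are recorded, so the gap lies in the analysis and not in the design.
- A reader might infer that the randomised comparison is biased by noise. Routine treatment, including the benzodiazepine taper, is common to all arms, so shifts in drug state should be largely shared and enter the time effect. With equal retained trials the false-positive rate stayed at about 5%. Nothing in the protocol shows that counts will differ by arm, and it specifies artifact removal and an impedance limit.

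It is also fair to say that research question 3 asks only whether EEG changes occur. A general change would answer it as worded; it would not support a conclusion about alcohol craving. Peak detection is an established measure and supplies latency, which is a reason to keep it as secondary.

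**Conclusion.** The point holds in a limited form. As specified, the EEG analysis does not isolate alcohol-cue reactivity, because image type enters neither as a factor nor as a contrast while the rationale depends on it. That follows from the text and needs no assumed figure.

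The peak measure is a separate weakness. The direction of its bias is general. Its size, about 1 to 2 µV on a 5 µV signal when retained trials rise from 20 to 60 or 80, rests on assumed amplitude, noise, window and trial counts. It bears mainly on before-after readings, the time effects and any EEG comparison of patients with healthy controls. The arm comparison is biased only if noise or retained trials differ by arm.

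EEG is a secondary outcome. The change is worth making because the data are already to be collected, but it does not touch the primary analysis or the sample size.

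**What to change.** In ERP detection, item (3): confirm that segments are averaged by image type. Measure N200 and P300 as mean amplitude in windows and at electrodes fixed before unblinding, and keep peak latency as secondary.

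In Data analysis: give EEG its own sentence. Make the outcome the within-patient alcohol-minus-neutral difference in mean amplitude, or add image type as a within-subject factor and test its interaction with group. Compare arms at weeks 2 and 8 with the baseline value as covariate. Report retained trials per image type, visit and arm, so that a reader can judge whether noise was balanced.

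Cost: wording only, with the same recordings, stimuli and software. Latency moves to a secondary place, and the difference will be less precise than the raw amplitude if the two conditions correlate below 0.5 within patients.
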